### Timeline

The recruitment began in October 2018, and the intervention period will be ending in June 2020. Figure 2 shows the schedule of enrollment, interventions and assessments.

**Fig. 2 Fig2:**
[figure not shown]
The schedule of enrollment, intervention and assessments. Abbreviations: *PLI* plaque index, *PD* probing depth, *CAL* clinical attachment loss, *BI* bleeding index, *FI* furcation involvement, *VAS* Visual Analogue Scale/Score

### Data collection and management

The data of the patients will be documented on both spreadsheets and databases. The statistical analysis will be performed by two experimenters independently.

### Statistical analysis

A Shapiro-Wilk test and Levene variance homogeneity test will be performed to test the normality and variance equality, respectively. Continuous normally distributed data will be expressed as mean ± standard deviation (SD), and non-normally distributed data as median (lower to upper quartile). A paired-samples *T* test or two-related-samples test will be used to identify any differences between groups. Statistical significance difference will be set as *P* value of less than 0.05. Data analyses will be performed using SPSS software.

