## Methods/design

### Overview

The study is a prospective, single-center, split-mouth randomized controlled trial. Forty patients who have periodontitis and are in need of periodontal treatment will be recruited. The assessments, interventions and follow-ups will be performed at Peking University School and Hospital of Stomatology (Beijing, China). This study has been approved by the Ethics Committee of Peking University School and Hospital of Stomatology (PKUSSIRB-201734032) and registered in the International Clinical Trials Registry Platform (ICTRP) under the ID: ChiCTR1800017122.

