### Groups, randomization and blinding

An experienced periodontist is going to perform the periodontitis disease diagnostic process according to clinical and radiographic examination. The randomization sequence and allocation concealment (placed in sealed envelopes) were performed by a professor in the absence of the working investigators; one quadrant of the upper and lower teeth is the test group and the other quadrant is the control group. Test group: ultrasonic subgingival scaling combined with manual root planing. Control group: ultrasonic subgingival debridement. All subjects will be treated by one experienced and calibrated therapist who does not partake in the allocation, examination, or statistical analysis. The treatment plan and grouping will be confidential to the examiner and statistical analyst.

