### Examination

#### Baseline examination

After the subjects have been included, plaque index (PLI), probing depth (PD), clinical attachment loss (CAL), bleeding index (BI), furcation involvement (FI) and mobility are tested before treatment by a calibrated examiner (not the therapist) who has been trained to adequate levels of accuracy and reproducibility.

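### The paired comparison names no baseline adjustment although the outcomes are measured before treatment, and it is accompanied by Levene's test, which a paired design does not need

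*Protocol article*

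**What the plan says.** The Overview of the protocol article describes a "prospective, single-center, split-mouth randomized controlled trial". Under Groups, randomization and blinding, "one quadrant of the upper and lower teeth is the test group and the other quadrant is the control group", so each patient supplies both arms.

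Under Baseline examination, six measures including PD, CAL and BI "are tested before treatment by a calibrated examiner". The Follow-up section repeats them at weeks 4, 12 and 24. The Interventions section places the full periodontal assessment before the allocation of sides. PD, CAL and BI are the primary parameters.

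The Statistical analysis section opens with pretests: "A Shapiro-Wilk test and Levene variance homogeneity test will be performed to test the normality and variance equality, respectively". It then links normality to how data are summarised: "Continuous normally distributed data will be expressed as mean ± standard deviation (SD), and non-normally distributed data as median (lower to upper quartile"). For the comparison of arms, a paired t test or "two-related-samples test will be used to identify any differences between groups". It names no covariate, does not say whether follow-up values or changes from baseline are compared, and gives no rule for choosing between the two tests.

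**The concern.** There are two separate issues.

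**Baseline.** The two sides of a mouth are seldom equally diseased. Where they differ before treatment, part of that difference is likely to persist at follow-up and add noise to the comparison of arms. The baseline values that could remove this noise are already being collected, but the stated method gives them no role.

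**Pretests.** Levene's test compares the variances of independent groups. Here the two groups are two sides of the same mouths. A paired t test works on one difference per patient and makes no assumption that the two sides have equal variances. Its normality assumption concerns those differences, not the raw values of each arm. The section does not say to which values the Shapiro-Wilk test will be applied.

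At stake are the width of the confidence interval for the arm effect and whether one primary analysis is fixed in advance.

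**Working it through.** **Inputs from the article (Sample size):** PD difference δ = 0.3 mm, within-group SD σ = 0.2 mm, α = 0.05 (the formula uses α/2, so two-sided), power 90%, loss to follow-up 10%, 40 subjects. Evaluable pairs: 40 × 0.9 = 36.

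**Assumed:** r, the correlation between the baseline and follow-up side differences, shown from 0 to 0.7; and an SD of the paired follow-up difference of 0.2 mm. The second is what σ = 0.2 gives at a within-patient correlation of 0.5: 0.2 × √(2 × (1 − 0.5)) = 0.2.

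**The plan's own figure.** The article gives no figure for the precision of the paired analysis. Its sample-size formula is for two independent groups. With equal allocation fractions of 0.5 (my reading), [(1.960 + 1.282) × 0.2/0.3]² × (1/0.5 + 1/0.5) = 4.67 × 4 = 18.68. That is close to the stated 18, but as a total and not per group. This is a separate matter; I use that section only for δ, σ and the number of patients.

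**Step 1: gain from baseline adjustment.** Let d0 and d1 be a patient's test-minus-control difference at baseline and at follow-up, with equal variances. Relative to analysing d1 alone, the large-sample variance of the arm effect is 2(1 − r) for the change d1 − d0 and 1 − r² for d1 adjusted for d0. The detectable difference at 90% power with 36 pairs is (1.960 + 1.282) × 0.2 × √(relative variance)/√36.

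| r | change score | adjusted | detectable, unadjusted (mm) | detectable, adjusted (mm) |
|---|---|---|---|---|
| 0 | 2.0 | 1.00 | 0.108 | 0.108 |
| 0.3 | 1.4 | 0.91 | 0.108 | 0.103 |
| 0.5 | 1.0 | 0.75 | 0.108 | 0.094 |
| 0.7 | 0.6 | 0.51 | 0.108 | 0.077 |

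Since 1 − r² ≤ 1 and 2(1 − r) − (1 − r²) = (1 − r)² ≥ 0, adjustment is never worse than either alternative in large samples. In sample-size terms, 1/0.91 = 1.10, 1/0.75 = 1.33 and 1/0.51 = 1.96, so the gain is worth 10%, 33% and 96% more patients.

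**Step 2: small-sample cost.** Estimating one slope from n pairs multiplies the variance by about (n − 2)/(n − 3) when baseline differences are normal. At n = 36 this is 34/33 = 1.03. Adjustment therefore costs about 3% if r = 0 and breaks even where 1 − r² = 33/34, that is, at r of about 0.17.

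**Step 3: does Levene's test tell the analyst anything?** In a simulation of 10,000 null trials with 36 normal pairs and one side's SD twice the other's, Levene's test rejected in 97% of runs, while the plain paired t test kept a type I error of 0.049. The screen fires and the test that it is meant to protect is unaffected.

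**Step 4: would letting the pretests pick the test do harm?** Simulating a paired t test if both pretests pass and the Wilcoxon signed-rank test otherwise gave type I errors of 0.049 (normal, equal SDs), 0.048 (SD ratio 2) and 0.051 (skewed values in each arm). The paired differences were symmetric in all three settings.

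**Step 5: power on the plan's own inputs.** With δ = 0.3 and σ = 0.2, a paired t test needs 12, 9, 7 and 6 pairs for 90% power at within-patient correlations of 0, 0.3, 0.5 and 0.7. About 36 are expected.

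**The case against.** The strongest reply is that the stated test is sound. Sides are randomised, so a chance baseline difference between them does not bias an unadjusted patient-level paired test; it is already reflected in the standard error. Step 5 shows that PD power is not at risk on the article's inputs, and Step 4 shows no loss of type I error control. Covariates may also be specified in an analysis plan that is not shown. All of this stands, and it limits the point to one of precision and of wording.

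A reader might infer more than the text supports:

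- **That baseline is ignored.** The article does not say whether follow-up values or changes are tested, and a paired test on changes would use baseline. What can be said is that no adjustment is named and the analysed quantity is left open.
- **That the pretests choose the test.** This is a natural reading, but normality is tied explicitly only to how data are summarised.
- **That tests are run separately at each visit.** This is not written.
- **That sites or quadrants are counted as independent pairs.** Nothing makes them the unit of analysis, and the Sample size section counts subjects. A design-effect calculation would address an analysis that nobody has proposed.

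The reply does not rescue Levene's test. The article itself names it for a paired design, so it cannot be put down to detail left elsewhere.

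**Conclusion.** The point holds in a limited form. Levene's test is misplaced on the face of the text, and two alternative tests are offered without a rule for choosing between them. The named comparison also makes no stated use of baseline values that are already being collected. The trial's validity is not in question.

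The size of the lost precision depends on r, which the documents do not give: nothing at r = 0 (with a cost of about 3% for the extra slope), 9% of the variance at 0.3, 25% at 0.5 and 49% at 0.7. This r is the correlation of side differences, after pairing has removed each patient's overall severity, so it need not be as high as the correlation of raw PD values over time. The figures compare with an unadjusted follow-up difference and assume equal variances at baseline and follow-up. Against a change score the gain is larger at low r and smaller at high r. The article gives δ and σ for PD only, so whether CAL and BI also have power to spare cannot be judged from it. The change is worth making because it costs almost nothing.

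**What to change.** 1. For each patient, average each primary outcome over the sites of each arm, at baseline and at follow-up.
2. Regress the week-24 test-minus-control difference on the baseline test-minus-control difference. Leave the baseline difference measured from zero and do not centre it at its sample mean, so that the intercept is the arm effect for sides that start equal. Report the intercept with its 95% confidence interval. Week 24 is proposed here as the last visit; the article names no primary visit.
3. State this as the single primary analysis in place of the choice between two tests.
4. Delete Levene's test. Check normality on the residuals of this regression of within-patient differences, and give the Wilcoxon signed-rank test on those differences as a sensitivity analysis.
5. If a mixed model over jaws and visits is preferred, include random effects for patient-by-arm and for quadrant (patient-by-jaw-by-side). Random effects for patient and patient-by-jaw alone cancel out of the side contrast. The model would then treat a quadrant's repeated visits, and a patient's upper and lower side differences, as independent.

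The cost is a few sentences in the analysis plan, slightly more analysis work and one degree of freedom. No new data are needed.

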### Ethical considerations

#### Ethical approval

The trial has been approved by the Ethics Committee of Peking University School and Hospital of Stomatology (PKUSSIRB-201734032). Before subjects are officially recruited into this study, they will be given a study information sheet and will be asked to sign a consent form.

### Withdrawal

Subjects will be informed that they have the right to withdraw from this trial at any time without providing a reason. If the withdrawal occurs, treatment will also be provided to the subject.

### Dissemination of results

The results of this trial will be saved at the International Clinical Trials Registry Platform (ICTRP) and published in an international peer-reviewed journal which will allow anyone access to obtain the results.

## Discussion

Periodontitis is strongly associated with the presence of bacterial biofilms and dental calculus on root surfaces. Hence, the ultimate goal of nonsurgical pocket/root instrumentation is to render the root free from microbial deposits and calculus. The success of periodontal treatment depends on the removal of deposits from the root surface [27–30]. All kinds of studies performed in different models and under different conditions have indicated that neither manual nor mechanical instruments are superior in removing subgingival deposits [31–37]. There was no significant difference in the changes of PD, CAL and BOP between manual subgingival debridement and ultrasonic subgingival debridement.

Previous studies demonstrated that hand instrumentation curettage created the smoothest root surface, whereas mechanical instruments, such as the ultrasonic scaler, tended to roughen the root surface [38]. Cobb found that manual curettes were more technique-sensitive and time-consuming [39]. The old concept of infected cementum removal in order to provide the root surface biocompatible for soft tissue healing [11, 12] has been questioned by various studies [15, 16]. The utilization of ultrasonic devices for subgingival debridement offers a less aggressive and a more comfortable therapeutic method for both the patient and therapist. But, some research has shown that the comparison between manual instruments and ultrasonic scalers did not show an advantage over machine-driven instruments [20], and tissue trauma was similar in both instruments [40]. Therefore, the necessity of manual root planing cannot be completely denied. Hand instrumentation has been recommended to smooth the root surface after ultrasonic debridement as the final finishing procedure in the treatment of periodontitis-affected roots [41]. At present, root planing is no longer used to emphasize the deliberate removal of cementum, but to contribute to the removal of subgingival plaque.

This study thus intends to evaluate in vivo the effectiveness of ultrasonic subgingival scaling combined with manual root planing and ultrasonic subgingival debridement alone in the nonsurgical treatment of periodontitis with a split-mouth design after 1, 3 and 6 months. We hope that the results could lead to an advanced treatment strategy of periodontitis with an ideal clinical outcome.

### Trial status

The trial has been registered at International Clinical Trials Registry Platform (ICTRP) under the identifier number ChiCTR1800017122 on 12 July 2018. The recruitment began in October 2018 and will be completed in June 2020.

## Data Availability

Not applicable

## Abbreviations

AgP: Aggressive periodontitis
BI: Bleeding index
CAL: Clinical attachment loss
CP: Chronic periodontitis
FI: Furcation involvement
ICTRP: International Clinical Trials Registry Platform
PD: Probing depth
PLI: Plaque index
SD: Mean ± standard deviation
VAS: Visual Analog Scale/Score
